**3. Methods**

**3.1. Subjects**

**T**he pancreatic cancer patients with cachexia (n=10) and without cachexia (n=10)

- Control : PS 0-2, Alb ≧ 3.5mg/dL, Anorexia Gr 0-1, Weight loss < 5% over past 6 months
- Cachexia : PS 1-4, Anorexia Gr1-4, Weight loss > 10% over past 6 months

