**3.3 Criteria for subject enrollment**

**3.3.1. Eligibility criteria**

1) Patients histologically confirmed adenocarcinoma or adenosquamous carcinoma of the pancreas.

2) Locally advancer or metastatic pancreatic cancer (UICCC TNM classification Stage IVA-IVB).

3) (a) Control: PS 0-2, Alb ≧ 3.5mg/dL, Anorexia Gr 0-1 (NCI-CTC ver.3), Weight loss < 5% over past 6 months

(b) Cachexia: PS 1-4, Anorexia Gr1-4, Weight loss > 10% over past 6 months

4) Patients 20 years of age or older.

5) Patients with adequate organ function as follows:

Liver function: AST and ALT less than 2.5 times of ULN.

Total bilirubin value less than 1.5 times of ULN.

Renal function: Serum creatinine level less than 1.5 times of ULN.

6) Patients from whom written informed consent for participation in the study is obtained.

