**4. Evaluation items**

1) Patient characteristics: gender, age at time of registration, date of birth, and patient identification number.

2) General findings: Performance status, height, weight and vital signs.

3) Tumor findings: pathological diagnosis, and clinical stage (TNM classification).

4) Hematology findings: CBC, TP, Alb, T-Bil, AST, ALT, LDH, Amy, BUN, Cr, T-Chol, LDL, HDL, TG, CRP, Glu, HbA1c and Tumor markers including CEA, CA19-9, and DUPAN-2.

5) Concomitant medications.

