**5. Endpoint and Statistical considerations**

**5.1. Endpoint**

Primary endpoint：identification of cachexia-related metabolites by metabolomics.

Secondary endpoints：intra-day variation in the metabolites involved in cachexia; changes in the level of serological markers involved in cachexia, such as inflammatory cytokines (e.g. IL-6, TNFα) and leptin, in the presence or absence of cachexia; and changes in QOL survey results in the presence or absence of cachexia.

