**5.3. Statistical analysis**

Data are expressed as the mean ± standard error. Levels of serological markers and metabolites between the cohorts with and without cachexia were compared using the Mann-Whitney U test or Wilcoxon Signed-Rank test. Kruskal-Wallis multiple comparison (z-test) with bonferroni correction was then used to compare values for each metabolite across all 4 time points tested to determine if there are intra-day variances in the metabolite. Survival time was estimated using the Kaplan-Meier method.

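### The primary metabolite comparison is unadjusted in two non-randomised, unmatched cohorts of 10, so any age or sex difference between them can be read as a cachexia effect

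*Protocol*

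**What the plan says.** The primary endpoint (Protocol, 5.1) is "identification of cachexia-related metabolites by metabolomics". The test that decides which metabolites qualify is in 5.3: "Levels of serological markers and metabolites between the cohorts with and without cachexia were compared using the Mann-Whitney U test", with the Wilcoxon signed-rank test named as the alternative.

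The cohorts are formed by clinical status. The cachexia criterion in 3.3.1 reads "Cachexia: PS 1-4, Anorexia Gr1-4, Weight loss > 10% over past 6 months"; controls are defined by performance status, albumin, anorexia grade and weight loss. The only limit on age is "Patients 20 years of age or older", and there is none on sex. Nothing in the protocol matches, stratifies or balances the cohorts on either.

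Both variables are collected; the first evaluation item in section 4 is "Patient characteristics: gender, age at time of registration, date of birth, and patient identification number". Section 5.2 calls the study exploratory, bases 10 per group on precedent, and allows the analysis method to change if a more useful one is found. It names no covariate.

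**The concern.** The endpoint is a list of metabolites, and confounding puts wrong entries on such a list. In a non-randomised comparison nothing ensures that the cohorts have similar age and sex distributions. If they do not, a rank test cannot tell a metabolite that differs because of cachexia from one that differs because one cohort is older or has more men.

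Age and sex are the natural pair to adjust for. Both are fixed before the illness and cannot result from cachexia, so adjusting for them removes no part of a cachexia effect. Performance status, anorexia and weight loss define the cohorts and do not have that property.

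There is a second, smaller matter. Where age and sex explain a good part of a metabolite's variance, leaving them out leaves noise that 10 v 10 can ill afford.

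**Working it through.** **Inputs from the protocol.** Two cohorts of 10, not randomised; age and sex recorded; an unadjusted rank test. The protocol has no alpha, effect size, SD or age and sex distribution, so it has no figure of its own to reproduce.

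**Assumptions.** Two-sided 0.05 per metabolite and normal data. Level = δ·cohort + βs·sex + βa·age + error, with error SD 1 and age in SD units. Two tests are compared by simulation:
- exact Mann-Whitney, which rejects at U ≤ 23 and has actual size 0.043;
- a linear model on ranks with cohort, sex and age, with 20 − 4 = 16 residual degrees of freedom instead of 18.

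**Step 1: false listing when cachexia has no effect (δ = 0).** The spurious cohort shift is βa × age gap + βs × difference in the proportion of men.

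| Imbalance | Spurious shift (SD) | Unadjusted | Adjusted |
|---|---|---|---|
| Age gap 0.5 SD, βa 0.5 | 0.5 × 0.5 = 0.25 | 6–7% | about 5% |
| Age gap 1 SD, βa 0.5 | 0.5 × 1 = 0.5 | 13–14% | 5–6% |
| The same, plus 8 v 5 men of 10, βs 1 | 0.5 + 1 × 0.3 = 0.8 | about 24% | about 6% |

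A second set of runs fixed R2, the share of variance due to age and sex, split equally between them:
- Age gap 0.5 SD and one sex at 70% v 40%: the unadjusted rate is 7%, 14% and 19% at R2 of 10%, 30% and 50%.
- Age gap 1 SD and 80% v 30%: 14%, 36% and 54%.
- The model on ranks stays at 5–6% in the first setting and at 6–7% in the second, more extreme one.

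**Step 2: how large are chance imbalances?** The SD of the age gap is √(1/10 + 1/10) = 0.447. So P(gap ≥ 0.5 SD) = 2Φ(−1.118) = 0.26, and P(gap ≥ 1 SD) = 2Φ(−2.236) = 0.025. For two independent Binomial(10, 0.55) counts of men, P(difference ≥ 3) = 0.26 and P(difference ≥ 4) = 0.11. Averaged over chance imbalance alone, the unadjusted test keeps its size, at about 4–5%.

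**Step 3: power with cohorts balanced in expectation, δ = 1.4 SD.** With equal numbers of each sex, R2 = (0.25βs² + βa²) / (1 + 0.25βs² + βa²).

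| βs, βa | R2 | Unadjusted | Adjusted |
|---|---|---|---|
| 0, 0 | 0 | 80–81% | 78% |
| weak dependence | about 6% | 78% | 77% |
| 1, 0.3 | 0.34/1.34 = 25% | 67–68% | 75–77% |
| 1, 0.5 | 0.50/1.50 = 33% | 63% | 75% |
| 1.5, 0.5 | 0.8125/1.8125 = 45% | 54–55% | 75% |

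The adjusted test here has size 0.050–0.055, against 0.043 for the exact test. With the sizes matched, its power at R2 = 0 is about 75–76%, the tests are about level near R2 11% (75.3% unadjusted v 74.6% adjusted), and the gain in the third row falls to 6 points (67.2% v 73.2%). The R2-based runs, with a shift of 1.25 SD and sizes not matched, agree: 71% v 70% at R2 5%, 71% v 72% at 10%, 71% v 82% at 30%.

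**Step 4: power under imbalance.** With a shift of 1.25 SD, R2 10%, an age gap of 0.5 SD and 70% v 40%, the unadjusted test rejects in 86% of runs when the covariates act with the cachexia effect, against 68% for the model on ranks. The excess is bias. When they act against it, the figures are 52% and 64%.

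**The case against.** The best case for the plan has four parts.

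- **The cohorts may not differ.** Performance status, anorexia, weight loss and albumin are not shown to select on age or sex, and a 1 SD age gap arises by chance in only about 2.5% of samples. Without a systematic difference the unadjusted test holds its size. This stands. A reader might infer that the test as planned has an inflated error rate, but the documents do not support that: the inflation depends on an imbalance that they neither show nor exclude.
- **Adjustment does not always help.** A reader might infer that power is lost for every metabolite that depends on age or sex. It is not. At an R2 of about 5–6% there is no gain, and with test sizes matched the break-even is near 11%. The documents give no basis for assuming R2 of 25–45%.
- **Adjustment costs more than it first appears.** With sizes matched, the loss when neither covariate matters is about 4–5 points rather than 2. This stands too.
- **The study is exploratory, methods may be altered, and an analysis plan may exist.** This lowers the severity but does not answer the point. The protocol does not leave the primary comparison open; it names an unadjusted test. The permission in 5.2 names no covariate and no trigger, and a change made after seeing the data would be post hoc.

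**Conclusion.** The point holds, and rests mainly on confounding. Section 5.3 fixes an unadjusted comparison of two non-randomised, unmatched cohorts of 10, while two harmless covariates are already collected. If the cohorts differ in age or sex, the primary list can contain metabolites that only track age or sex: about 13–14% false positives per metabolite in the 1 SD age-gap case and about 24% with a sex imbalance as well, but only 6–7% for a 0.5 SD age gap alone. The adjusted test gives about 5–6% in these cases.

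The power argument is secondary. It applies to metabolites for which age and sex explain more than roughly 10% of the variance.

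Alpha, the cachexia shift, the covariate effects and the imbalance are all assumed, so these figures show what could happen and do not predict this study's results. The change is worth making, but its absence is not fatal to an exploratory study.

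**What to change.** In 5.3, state that each metabolite is compared between cohorts by a rank-based ANCOVA with cohort, age and sex, and with no further covariates given 20 patients. Report the plain Mann-Whitney result beside it, and tabulate age and sex by cohort. Call a metabolite cachexia-related only if the cohort difference persists after adjustment.

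The cost is a few sentences and no new data. If neither covariate matters, power falls by about 2 to 5 points (from 80% to about 75–78%, depending on whether test sizes are matched). The adjusted test also runs slightly above nominal size, at about 5–6%, and reached 7% in the most extreme imbalance tried.

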**3.4. Collection of samples**

**3.4.1. Serum samples for metabolomics and serum markers**

Blood samples will be collected (approximately 5 ml of whole blood) at 6:30 AM, 11:30 AM, 4:30 PM, and 9:30 PM to analyze the intra-day variation. After collection of whole blood, samples were allowed to clot at room temperature, and serum was separated by centrifugation at 3,000×g for 10 min at 4 °C and stored at -80 °C until use.

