**5.2. Rationale for sample size**

The present study featured 10 subjects per group, as although this study was exploratory in nature and therefore involved no statistical rationale for sample size calculation, preceding studies on metabolomics have indicated significant results with a sample size of approximately 10 subjects per group. However, if a more useful analysis method found is found that may be implemented in the study, the analysis methods may be altered and the necessary sample size recalculated.

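### Section 5.3 tests intra-day variation with Kruskal-Wallis, which ignores that the four samples come from the same patient and loses power for moderate rhythms when patients differ markedly

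*Protocol*

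**What the plan says.** Section 3.4.1 has blood drawn "at 6:30 AM, 11:30 AM, 4:30 PM, and 9:30 PM to analyze the intra-day variation". Section 5.1 lists as a secondary endpoint the "intra-day variation in the metabolites involved in cachexia". Section 5.3 names the test: "Kruskal-Wallis multiple comparison (z-test) with bonferroni correction was then used to compare values for each metabolite across all 4 time points tested". Its stated purpose is "to determine if there are intra-day variances in the metabolite".

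On size, section 5.2 says "The present study featured 10 subjects per group" and that the study "involved no statistical rationale for sample size calculation". The same section allows that "the analysis methods may be altered and the necessary sample size recalculated" should a more useful method be found.

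Nothing in section 5.3 links the four values of one patient. The only paired test it names, the Wilcoxon signed-rank test, is attached to the comparison of patients with and without cachexia, who are different people. The section does not say whether the time comparison is made within each cohort or on all 20 patients.

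**The concern.** Kruskal-Wallis ranks all values together and judges the differences between time points against the whole spread of those values. When the same patients supply all four time points, stable differences between patients form part of that spread, although they cancel out of any within-patient comparison over time. The reference distribution is then too wide for the statistic. The actual error rate falls below nominal and power falls with it. The Bonferroni-corrected z-tests are unpaired in the same way.

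At stake is the reading of a negative result. A metabolite with a moderate daily rhythm could be reported as having none because the test set the patient aside, and the p-value could not be taken at face value because its calibration depends on an unstated correlation. This is not a detail left to a later analysis plan: the protocol names the test, and the named test does not fit the design.

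**Working it through.** **Inputs from the protocol.** There are k = 4 times (section 3.4.1), and n = 10 per cohort or 20 if pooled (section 5.2). It states no alpha, effect size, SD, ICC or power, so there is no figure of its own to reproduce.

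**Assumptions.** Omnibus alpha 0.05; normal data with total SD 1 (between plus within patients) and equal correlation ICC between any two times; time profile d × (−0.5, 0, 0.5, 0), where d is the peak-to-trough swing in total SD. ICC is varied from 0 to 0.9. Each setting has 20,000 simulated trials.

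**Why the test is conservative.** For two time-point means from the same n patients, the variance of the difference is 2σ²(1 − ICC)/n. An independent-groups test takes it as 2σ²/n. The ratio of true to assumed variance is 1 − ICC: 0.5 at ICC 0.5 and 0.2 at ICC 0.8.

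**Statistics compared,** both referred to chi-square with 3 df:
- Kruskal-Wallis: H = 12/[N(N+1)] × Σ R_j²/n − 3(N+1), with N = 4n and ranks taken over all N values.
- Friedman: Q = 12/[nk(k+1)] × Σ R_j² − 3n(k+1), with ranks 1 to 4 taken within each patient.

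**Results, n = 10** (per cent of trials rejecting; KW = Kruskal-Wallis, Fr = Friedman):

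| ICC | Type I KW | Type I Fr | d = 0.8 KW | d = 0.8 Fr | d = 1.5 KW | d = 1.5 Fr |
|---|---|---|---|---|---|---|
| 0 | 4.4 | 4.4 | 24.0 | 19.9 | 72.4 | 60.9 |
| 0.3 | 1.6 | 4.7 | 17.1 | 26.9 | 71.3 | 77.4 |
| 0.5 | 0.5 | 4.7 | 12.9 | 36.8 | 71.0 | 89.5 |
| 0.7 | 0.03 | 4.4 | 9.3 | 58.5 | 72.1 | 98.8 |
| 0.8 | 0.01 | 4.9 | 7.7 | 77.3 | 72.1 | 99.9 |

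Repeat simulations agree to within about two percentage points on power. They put the Kruskal-Wallis type I error at 1.2% to 1.6% for ICC 0.3 and at no more than about 0.1% for ICC 0.7.

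**Results, n = 20 pooled, d = 0.8** (KW against Fr): 44.0% against 55.4% at ICC 0.3; 40.0% against 70.9% at 0.5; 35.9% against 91.4% at 0.7; 33.6% against 98.5% at 0.8.

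**At equal footing.** With d set so that Friedman has 80% power at n = 10, Kruskal-Wallis has 90% (ICC 0), 75% (0.3), 54% (0.5), 23% (0.7), 9% (0.8) and 1% (0.9). The relative loss at ICC 0.5 is (80 − 54)/80, about a third; at ICC 0.8 it is (80 − 9)/80, about nine tenths.

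**Follow-up tests.** Four times give 4 × 3/2 = 6 pairs, so each is tested at 0.05/6 = 0.0083. For the peak-trough pair (n = 10, d = 0.8; 4,000 trials), the unpaired z-test has power 11% / 9% / 8% at ICC 0.5 / 0.7 / 0.8, against 21% / 39% / 60% for the signed-rank test. The smallest two-sided exact signed-rank p-value with 10 patients is 2/2¹⁰ = 0.002, so the corrected threshold can be reached.

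**The case against.** That each patient gives all four samples is not stated word for word. With 10 subjects per group and an intra-day aim, though, no other reading is plausible.

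The study is exploratory, the endpoint is secondary, the comparison of cohorts for the primary endpoint does not use this test, and the error does not create false rhythms. All of that stands and limits the severity. The general permission in section 5.2 to change methods does not repair the rule, because it names no paired test for the time points.

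A reader might infer that most real within-day variation will be missed. The documents do not support this: the loss depends on an ICC and a rhythm size that they do not give. At ICC 0.3 the gap is modest, at ICC 0 Kruskal-Wallis does slightly better, and a 1.5 SD swing is mostly found at every ICC. Part of the low power also comes from the sample size: at ICC 0.5, n = 10 and d = 0.8, Friedman itself finds only 37%.

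A reader might also take it as known that differences between patients are the largest source of variation in metabolite levels. The protocol gives no variance components, so that is an assumption.

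Finally, a reader might infer that the plan omits a required comparison of the daily pattern between cohorts. Section 2.1 says only that circadian effects may need to be taken into account, and the purpose given in section 5.3 is whether intra-day variation exists. A group-by-time test would be an added objective.

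**Conclusion.** Wrong as written, and it should be fixed; the severity is moderate, given a secondary endpoint in an exploratory study and an error in the conservative direction. An independent-groups test is applied to repeated measures, and nothing elsewhere in the protocol restores the pairing.

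The size is conditional. If the ICC is about 0.5 or more, Kruskal-Wallis runs at a true level of about 0.5% or below and gives up from a third to nearly all of the power of a paired test for moderate rhythms. In that range a null result cannot be read as absence of intra-day variation. At low ICC, or for large rhythms, the practical harm is small. These figures rest on normal data, equal correlation between times, alpha 0.05 and assumed ICCs and swings. The direction of the error rests only on values from the same patient being positively correlated.

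**What to change.** In section 5.3, replace Kruskal-Wallis and the z-tests with the Friedman test within each cohort, followed by Wilcoxon signed-rank tests on the six within-patient pairs of time points, Bonferroni-corrected. State that values are paired by patient.

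As an alternative, use a mixed model on log intensity with time as a fixed effect and patient as a random effect. This is a different, parametric analysis and not the equivalent of Friedman, but it keeps patients with a missing time point. A group-by-time comparison may be added if the difference in rhythm between cohorts is of interest; it is optional.

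The cost is a rewording, with no new patients or samples. The drawback of Friedman is that patients missing a time point drop out. In a cohort of 10 this matters: with 8 complete patients the smallest exact signed-rank p-value is 2/2⁸ = 0.0078, just under 0.0083; with 7 it is 2/2⁷ = 0.016, and no pair could then pass the correction.

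### Bonferroni over the time-point pairs is valid, but the Holm step-down would name slightly more of the differing pairs at the same family-wise error rate (minor)

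*Protocol*

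**What the plan says.** Section 5.3 plans a "Kruskal-Wallis multiple comparison (z-test) with bonferroni correction" and gives its purpose: to "compare values for each metabolite across all 4 time points tested to determine if there are intra-day variances in the metabolite". Section 3.4.1 sets the draws at "6:30 AM, 11:30 AM, 4:30 PM, and 9:30 PM to analyze the intra-day variation", so each patient contributes four values per metabolite. Section 3.1 plans 10 patients in each cohort. Section 5.1 lists "intra-day variation in the metabolites involved in cachexia" among the secondary endpoints, and section 5.2 calls the study "exploratory in nature and therefore involved no statistical rationale for sample size calculation".

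The protocol does not state a significance level, the number of comparisons in the family, an effect size, or whether the two cohorts are pooled for this analysis. It plans no simultaneous confidence intervals for the time-point comparisons.

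**The concern.** Bonferroni holds every pair to the threshold needed by the smallest p-value, even after some pairs have been rejected. Holm relaxes the threshold step by step and keeps the same error guarantee without any assumption about dependence between the tests. When more than one pair of times truly differs, Bonferroni can leave some of them undeclared that Holm would declare.

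With 10 patients per cohort, power for individual pairs is modest. What is at stake is how completely the report can say which times of day differ for a metabolite. Section 3.2 speaks of the pattern of metabolites as well as their intra-day variation, so this detail has some value.

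**Working it through.** There is no stated power, alpha or calculated sample size to reproduce, so the check compares the two corrections directly.

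**Inputs from the protocol.** 4 time points (5.3, 3.4.1); 10 patients per cohort, 20 in total (3.1); Bonferroni correction (5.3).

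**Assumed.** Family-wise alpha 0.05 two-sided; the family is the set of pairs within one metabolite; the planned z-test is a pairwise comparison of mean pooled ranks (Dunn type).

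**Step 1: number of pairs.** 4 × 3 / 2 = 6.

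**Step 2: thresholds.**
- Bonferroni: 0.05/6 = 0.00833 for every pair (z = 2.638).
- Holm, from smallest to largest p-value: 0.05/6, 0.05/5, 0.05/4, 0.05/3, 0.05/2, 0.05/1 = 0.00833, 0.0100, 0.0125, 0.0167, 0.025, 0.05, stopping at the first p-value that fails.

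**Step 3: what follows without simulation.**
- No Holm threshold is below 0.00833, so Holm rejects every pair that Bonferroni rejects.
- If k of the six null hypotheses are true, Holm's first false rejection can occur only at a threshold of at most 0.05/k. The chance of any false rejection is therefore at most k × 0.05/k = 0.05, the same bound as for Bonferroni.
- The first Holm threshold equals the Bonferroni threshold. If Bonferroni rejects no pair, Holm rejects none. The two always agree on whether any pair differs.

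**Step 4: size of the gain.** Simulation with 10 patients, patient SD 1, within-patient SD 1, and one time point shifted against the other three, so that three of the six pairs truly differ:

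| Pairwise test | Shift (within-patient SD) | Power per true pair, Bonferroni | Holm | Gain (points) |
|---|---|---|---|---|
| Planned z-test on pooled ranks | 1.5 | 23% | 25% | 2 |
| Planned z-test on pooled ranks | 2 | 53% | 58% | 5 |
| Paired signed-rank | 1.5 | 42% | 49% | 7 |
| Paired signed-rank | 2 | 72% | 80% | 8 |

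With signed-rank tests, the chance of finding all three true pairs rises from 15% to 24% (1.5 SD) and from 46% to 61% (2 SD).

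The probability of at least one rejection at 1.5 SD is 0.453 under both corrections with the z-test and 0.711 under both with signed-rank tests, as step 3 requires.

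**Step 5: sensitivity.** A second set of simulations used the planned z-test, within-patient correlation 0, 0.5 or 0.8, and shifts in units of the total SD of (0,0,0,1), (0,0,1,1) and (0,0.5,1,1.5).
- 10 patients: gain per true pair of about 1 to 3 points (for example 0.202 to 0.219, correlation 0.5, one time shifted).
- 20 patients: gain of about 3 to 8 points (for example 0.655 to 0.726, correlation 0.5, two times shifted).
- The largest simulated family-wise error was 0.041, for both corrections.

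**The case against.** The strongest case against the point is that Bonferroni is valid and simple, and gives the same answer to the question the section asks. The stated purpose is to establish whether a metabolite varies within the day. On that question Holm gains exactly nothing. The endpoint is secondary, the study is exploratory, and section 5.2 already allows the analysis methods to be changed if a more useful one is found. Bonferroni also has matching simultaneous confidence intervals, which Holm lacks in simple form. All of this stands, and it is why the point is minor. The interval argument carries little weight here, because section 5.3 plans no such intervals.

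Two stronger readings are tempting and neither is supported.

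- A reader might infer that Bonferroni causes varying metabolites to be reported as stable. It cannot do so relative to Holm, because both apply the same threshold to the smallest p-value.
- A reader might take the gains of 7 to 8 points as what this edit would deliver. Those figures belong to paired within-patient tests, which section 5.3 does not plan for the time-point comparison. Changing the correction alone leaves the Kruskal-Wallis z-test in place.

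The same sentence of the plan also applies a test for independent samples to repeated draws from the same patients. That is a separate and larger matter, and Holm does not address it. For scale, with 10 patients, correlation 0.5 and one time shifted by 1 total SD, the chance of declaring any pair was 0.399 with the planned test under either correction, while a Friedman test detected variation with probability 0.745.

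**Conclusion.** The point holds as a small efficiency gain and does not show an error in the plan. Bonferroni gives up power for the second and later differing pairs and none for detecting intra-day variation as such. The consequence is a less complete description of which sampling times differ.

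With the planned z-test, 10 patients and one time shifted by 1.5 to 2 within-patient SD, the gain is about 2 to 5 points per differing pair.

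Holm's dominance, its error control and the agreement on whether any pair differs hold for any family size and alpha. The percentages rest on assumed shifts, variance components, alpha 0.05 and six pairs, none of which the protocol states.

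**What to change.** In section 5.3, replace "with bonferroni correction" by wording such as: with Holm step-down correction over the six pairwise time-point comparisons for each metabolite. This also states the size of the family, which the section leaves to inference.

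The cost is one phrase. Holm is available in standard software and needs no extra data or patients. The only thing lost is a simple set of simultaneous confidence intervals, which the section does not plan.

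The larger gains in the table would also require the pairwise tests themselves to become within-patient tests. If that change is made, both edits can go in together, but the change of correction does not bring it about.

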**2. Background**

**2.1. Pancreatic cancer and cachexia**

Pancreatic cancer is the leading cause of cancer-related death. At the time of diagnosis, tumor resection with curative intent is only possible in 10%to 15% of subjects, leaving a large population with poor prognosis and limited therapeutic options. Overall, the 5-year survival rate is only about 4%.

Some patients with advanced or end-stage pancreatic cancer experience debilitating symptoms such as weight loss, emaciation, hypoproteinemia, and edema, also known as cachexia. These symptoms may be caused by changes in carbohydrate/protein metabolism experienced as the disease progresses. While secretion of inflammatory cytokines (IL1, IL6, TNF-α, TGF-β, etc.) and vascular endothelial growth factors (VEGFs) has been reported to be involved in the pathophysiology of cachexia, the precise mechanism of cachexia are unknown [1, 2].

Clarification of the mechanism of cachexia may require comparison of pathophysiological changes between cancer patients with and without cachexia. In addition, the physiology of living organisms is known to be affected by circadian rhythms. We think that effects of circadian rhythms may need to be considered in the evaluation of metabolic changes associated with cachexia [3, 4].

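### Section 5.3 answers the intra-day secondary endpoint only by a significance test that treats each patient's four draws as independent, and gives no within-patient change with its own uncertainty

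*Protocol*

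**What the plan says.** Section 5.1 makes "intra-day variation in the metabolites involved in cachexia" a secondary endpoint. Section 3.4.1 has every patient bled four times in the day, "at 6:30 AM, 11:30 AM, 4:30 PM, and 9:30 PM to analyze the intra-day variation". Section 2.1 gives the reason: "effects of circadian rhythms may need to be considered in the evaluation of metabolic changes associated with cachexia".

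Section 5.3 fixes the analysis: "Kruskal-Wallis multiple comparison (z-test) with bonferroni correction was then used to compare values for each metabolite across all 4 time points". The stated aim is "to determine if there are intra-day variances in the metabolite". The only summary is a general one: "Data are expressed as the mean ± standard error". No within-patient change, amplitude or interval is named.

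On size, section 5.2 says "The present study featured 10 subjects per group" and that the study "involved no statistical rationale for sample size calculation". Section 5.3 does not say whether the SE is taken per draw, or whether the time comparison is run per cohort or on all 20 patients. The protocol gives no alpha, target difference, SD or within-patient correlation.

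**The concern.** The purpose in section 2.1 calls for a size: how large is the change over the day beside a difference between cohorts? Section 5.3 returns a yes or no.

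Two features make that answer weak on the negative side. Kruskal-Wallis is an independent-samples test, so stable differences between patients stay in its noise although each patient could serve as their own control. And 10 patients per cohort give limited power for moderate swings even with a suitable test. The planned summary does not make up for this, because an SE per draw measures how patients differ from one another and not how precisely the change within a patient is known.

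At stake is the use of the result. A metabolite with a sizeable swing over the day could come out non-significant, be read as steady, and then be compared between cohorts as if the time of the draw did not matter.

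**Working it through.** The protocol states no power, alpha or effect size, so there is no figure of its own to reproduce. What follows is illustrative.

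**Inputs from the protocol:** 10 patients per cohort, 20 in all (5.2); four draws per patient (3.4.1); Kruskal-Wallis with Bonferroni-corrected z comparisons (5.3).

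**Assumed:** normal data; swings in units of the total SD at one draw; ICC = within-patient correlation, mainly 0.5; two-sided alpha 0.05.

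**1. Standard error of a change between two draws (SD = 1, n = 10, ICC = 0.5)**
- Two per-draw SEs combined as if independent: sqrt(2/n) = sqrt(2/10) = 0.447.
- From within-patient differences: sqrt(2(1-ICC)/n) = sqrt(2 × 0.5/10) = 0.316.
- Ratio: 1/sqrt(1-ICC) = 0.447/0.316 = 1.41.
- Range over ICC 0.3, 0.5, 0.7, 0.8, 0.9: 1.20, 1.41, 1.83, 2.24, 3.16. At ICC 0 the ratio is 1.

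**2. 95% half-width for one pair of draws, n = 10**
- From per-draw SEs: t(18) × 0.447 = 2.101 × 0.447 = 0.94 SD, whatever the ICC.
- From within-patient differences: t(9) × 0.316 = 2.262 × 0.316 = 0.72 SD at ICC 0.5 (about 0.70 on average over samples); 0.55 at ICC 0.7; 0.32 at ICC 0.9.
- Bonferroni over six pairs, ICC 0.5: the two-sided level is 0.05/6 = 0.0083, the t(9) value is 3.364, and 3.364 × 0.316 = 1.06 SD.

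**3. How often a real swing is non-significant (simulation, ICC 0.5; ranges run from one raised draw to a steady rise over the day)**

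| Patients | True swing | Kruskal-Wallis | Friedman (repeated-measures rank test) |
|---|---|---|---|
| 10 | 0.8 SD | about 75-85% | about 47-60% |
| 10 | 0.5 SD | 94-96% | about 78-83% |
| 20 | 0.8 SD | – | 12-23% |
| 20 | 0.5 SD | – | 53-65% |

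**4. Second profile (peak at the third draw, half-height on either side, 1 SD peak to trough)**
- n = 10: Kruskal-Wallis is significant in 25%, 22% and 21% of runs at ICC 0.5, 0.7 and 0.9. Bonferroni-corrected pairwise z-tests give 24%, 24% and 26%. Friedman gives 54%, 79% and 99.8%.
- n = 20: Kruskal-Wallis 70%, 70% and 73%; Friedman 89%, 99% and 100%.
- No swing, n = 10: Kruskal-Wallis rejects in 0.4%, 0.1% and 0.0% of runs, where 5% is nominal.

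The stated test therefore errs towards missing variation and not towards false positives. At ICC 0.5, changing the test alone still leaves about half of 0.8 SD swings undetected with 10 patients.

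**The case against.** A reader might infer three stronger things from section 5.3. The documents do not support them.

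- *Non-significant metabolites will be declared stable and draw time ignored.* No section says so. Section 5.3 has no rule for a non-significant result, and section 3.4.1 fixes the same clock times for everyone. The stated aim of the test invites the reading, but no more.
- *The change over the day is never estimated.* If means are shown per draw, subtracting them gives the mean change, and with complete data this equals the mean within-patient change. What is missing is its correct uncertainty.
- *Ten patients are too few whichever test is used.* That depends on an ICC the protocol does not give. At ICC 0.9 and a 1 SD swing, Friedman detects 99.8%.

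Other objections have weight. Mean ± SE is a general convention and suits the cohort comparison, where between-patient spread belongs; the 1.4-fold figure applies only if the SE is per draw and a reader combines two of them as independent. The largest miss rates come from using an independent-samples test on repeated draws, and pooling the cohorts would lower them. The study is exploratory, and intervals are often left to an analysis plan, which is not shown here.

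The last argument does not dispose of the point. Section 5.3 is not silent: it names the test and what the test is to decide, and that choice fits repeated draws badly. It does name a paired test, the Wilcoxon signed-rank, but attaches it to the comparison between cohorts. An exploratory label excuses low power; it does not make a null result informative.

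**Conclusion.** The point holds in this form. For a secondary endpoint measured four times in the same patients, section 5.3 gives a yes or no from a test that ignores the pairing, and it names no summary that carries the within-patient uncertainty of the change.

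Under the stated assumptions (ICC 0.5, n = 10, 0.8 SD swing) a null result arises in about 75-85% of studies with the stated test and about 47-60% with a repeated-measures rank test. A null result can thus be misread as no variation. That it will be misread is a risk, not something the plan lays down.

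The ratio 1/sqrt(1-ICC) is exact for equal variances, but its relevance rests on the SE being per draw. The miss rates rest on assumed correlations, swings and normal data. They fall if the cohorts are pooled and, for the repeated-measures test, if the ICC is higher.

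**What to change.** In section 5.3, for each metabolite and cohort:

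1. Report the mean within-patient change on the log scale for all six pairs of draws. Comparing only with 6:30 AM would leave differences between later draws unexamined.
2. Compute each interval from the within-patient differences and Bonferroni-adjust over the six pairs, in keeping with the correction section 5.3 already names. Without adjustment, even three intervals against 6:30 AM would flag about 13% of flat metabolites, against about 4.6% with Bonferroni over three.
3. State that a non-significant result is not reported as absence of intra-day variation.

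Classifying metabolites as stable against a preset margin is optional and not needed for the repair. At n = 10, ICC 0.5 and a 0.8 SD margin, a truly flat metabolite would pass in only about 5% of runs, even with unadjusted intervals against 6:30 AM.

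The cost is one paragraph and a little analysis of samples already planned; section 5.2 allows the methods to be altered. The downside is wide intervals for many metabolites: about 0.70 SD either side unadjusted at n = 10 and ICC 0.5, and about 1.06 SD after adjustment over six pairs.
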